### Participant Identification and Randomization

Participants in both groups will be randomly assigned a unique identification number, which will be used throughout the study to ensure anonymity and meet the inclusion criterion of randomization. Psychological assessments conducted at the rehabilitation center will be conducted through self-reported questionnaires, administered in a traditional pen-and-paper format, overseen by the institution’s psychologists, who will use only the assigned ID numbers during the digitization of all data. Control participants will complete all psychological tests in a self-reported computer-based format, using their ID numbers, which will be randomly assigned at the start of the monitoring period.

A secondary randomization process will be conducted to create k-clusters of data before training the ML algorithm. This step will also include the selection of test data for verification purposes, ensuring robust validation of the model.

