### Blinding

Due to the nature of this study, neither the participants nor the first group of research staff will be blinded to group assignments. However, the group allocation of participant ID clusters will remain concealed from the second group of researchers. This second group will be responsible for data management, training the ML algorithm with the predictive model, and conducting validation, verification, and testing of the highest-performing models.

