### Data Preprocessing

Databases and labeling will initially be managed using Microsoft Excel (version 2412), after which MATLAB (version 2025a, MathWorks, Inc) will be used for data preprocessing. This process will include data cleaning and preparation to ensure the dataset is suitable for ML training.

Feature selection will be done following a filter methodology after correlation analysis to assess the correlation with the target and statistical measures. All data obtained through the wearable device, psychological assessment and ESDC will be scaled through a *z*-score standardization for dimensionality reduction and integration across all modality.

The data will be divided into training, validation, and test datasets using a k-fold cross-validation approach. The dataset will be split into k folds, with 2 folds randomly selected: one for validation and another for testing. The remaining k-2 folds will be used for training. The number of folds will vary depending on the specific model, enabling a broader experimental variance and improved model evaluation.

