### Algorithms

Modeling will be conducted using MATLAB, with ANN serving as the base algorithm. Additional algorithms, including decision trees, random forests, and support vector machines, will be used for validation. This multialgorithm approach will facilitate a comprehensive comparison of predictive accuracy across various models.

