### Validation and Verification

All models and algorithms will undergo validation, verification, and testing using MATLAB’s tools for model evaluation and hyperparameter optimization. These processes will assess precision, performance, and recall metrics. Optimal model performance will be defined by achieving an area under the curve (AUC) of ≥0.80 and F2 score of ≥0.8.

The output categories will serve as benchmarks to evaluate the validity, reliability, and precision of the models. The validation dataset will be used to perform initial comparisons both within individual models of each algorithm and across different algorithms, replicating models with distinct architectures to refine performance.

For model verification, the test dataset will be used to determine final AUC and F2 scores. This final evaluation will confirm the models’ effectiveness as ML tools for predicting rehabilitation outcomes and informing clinical decision-making.

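### Letting the number of folds differ by model leaves no common validation or test set, so the ranking of algorithms is partly confounded with the data split

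*Protocol article*

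**What the plan says.** All references are to the protocol article.

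- **Data Preprocessing** describes the split: "The dataset will be split into k folds, with 2 folds randomly selected: one for validation and another for testing". It continues: "The remaining k-2 folds will be used for training". It closes with: "The number of folds will vary depending on the specific model, enabling a broader experimental variance and improved model evaluation".
- **Algorithms** makes the neural network the base algorithm and adds: "Additional algorithms, including decision trees, random forests, and support vector machines, will be used for validation". The purpose is given as: "This multialgorithm approach will facilitate a comprehensive comparison of predictive accuracy across various models".
- **Validation and Verification** states where the ranking happens: "The validation dataset will be used to perform initial comparisons both within individual models of each algorithm and across different algorithms". Final AUC and F2 then come from the test dataset. Both must reach 0.8.
- **Blinding** gives the second research team the task of "conducting validation, verification, and testing of the highest-performing models".
- **Participant Identification and Randomization** says: "A secondary randomization process will be conducted to create k-clusters of data before training the ML algorithm". It places the choice of test data at the same step.

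No section states a value of k, a partition shared by all models, or rotation through all folds.

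**The concern.** A comparison of algorithms is fair when each is trained on the same people and scored on the same people. Validation and Verification speaks of the validation dataset and the test dataset as though there were one of each. If k depends on the model, there cannot be.

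Three things then change together with the algorithm: how much data it learns from, how many people it is scored on, and which people those are. A difference in AUC between, say, the neural network and the random forest cannot be attributed to the algorithm alone.

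The stated reason for varying k is also the wrong way round. Extra variability in a score that is used to pick a winner makes the pick less reliable. At stake is which model goes forward to the final test and then to the graphical interface intended for clinical use.

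**Working it through.** **The plan's own figure.** There is none to reproduce. The protocol gives no k, fold size or precision for the AUC.

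**Inputs from the document.** At least 25 participants per group (Sample Size), so N=50 for SUD versus control and N=25 for outcomes among SUD patients. Relapse rate 60% (Introduction), so 15 relapsing and 10 not. One validation and one test fold of about N/k each; training share (k-2)/k (Data Preprocessing).

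**Assumptions, not in the document.** k=3, 5 and 10. True AUC 0.65 for every model. Binormal scores. Relapse treated as yes or no, although the Output section has three latency labels. Folds drawn at random without stratification, as the text describes.

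**Step 1: what changes with k.**

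| k | Training share (k-2)/k | Fold size, N=50 | Fold size, N=25 |
|---|---|---|---|
| 3 | 1/3 = 33% | 16 | 8 |
| 5 | 3/5 = 60% | 10 | 5 |
| 10 | 8/10 = 80% | 5 | 2 or 3 |

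Folds of different size cannot contain the same people.

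**Step 2: precision of one fold, SUD versus control, N=50, true AUC 0.65.** The simulated SD of the fold AUC is 0.14, 0.19 and 0.29 for k=3, 5 and 10. The chance that a single fold shows AUC of 0.80 or more is 16%, 25% and 35%.

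**Step 3: who wins among equally good models, N=50.** Each model is scored on its own random fold, the highest AUC wins, and ties are shared. A fair split of three would be 33% each.

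- k=3/5/10: about 28/33/40%.
- With four models at k=3/5/8/10: 17/21/29/33%. With k=5 for all four: 24 to 26% each.
- At true AUC 0.70 the four-model pattern persists at N=100 (17/22/29/32%) and N=200 (18/22/28/32%).

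**Step 4: SUD patients only, N=25, 60% relapse.** A model whose AUC cannot be computed cannot win.

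- k=3/5/10 with folds of 8, 5 and 3: about 32/34/34%, so no clear advantage for the smallest fold.
- A fold gives no AUC when all its members share one outcome. For 3 people: (C(15,3)+C(10,3))/C(25,3) = (455+120)/2300 = 25%. For 2 people: (C(15,2)+C(10,2))/C(25,2) = (105+45)/300 = 50%.

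**Step 5: what a common k alone achieves.** With four models, N=50 and true AUC 0.70, the winner's mean AUC is 0.88 under a common k=5 and 0.91 under varying k. It reaches 0.80 in 81% and 82% of runs. A common k makes the comparison fair but does not remove the optimism that comes from tiny folds.

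**The case against.** The strongest replies are these.

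1. **The text may intend ordinary cross-validation.** Data Preprocessing uses the term k-fold cross-validation, which normally rotates every fold. With rotation and pooled predictions, everyone is scored under any k and the fold-size effect largely vanishes. This stands as a possible intention, but the text describes one random pick of two folds and no rotation.
2. **The word model may mean a prediction task or an architecture, not an algorithm.** If k varied only by task, algorithms within a task could share folds. The sentence does not say so. If k varies by architecture, the comparisons within an algorithm are affected instead.
3. **A common test set may be planned.** The randomization section places cluster creation and choice of test data before training, which fits a single partition. A k that varies by model does not, so the two sections need reconciling.
4. **Final AUC and F2 come from a separate test fold.** This limits selection optimism, but only in part. The test fold also shrinks as k rises, so a model truly below 0.80 passes by chance more easily (16%, 25% and 35% in Step 2).
5. **Seed, stratification and paired testing belong in an analysis plan.** Agreed: their absence is not the point. The point is the explicit statement that k will vary.

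A reader might go further and infer that the noisiest split generally wins. The document does not support that as a general rule. For 25 SUD patients at true AUC 0.65, shares of 25/30/45% for k=3/5/10 appear only if both outcomes are forced into every fold; the unstratified folds described give about 32/34/34%. Nor does a poor model on a small fold usually beat a better one on a large fold. Even with both outcomes forced, a k=10 model with true AUC 0.60 strictly wins about 45% of draws against a k=3 model with true AUC 0.70, which strictly wins about 50%.

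**Conclusion.** The point holds as a defect in a stated rule. A model-specific k rules out common validation and test sets, so the planned ranking is partly confounded with the split, and the justification offered for varying k is mistaken. That conclusion needs no simulation.

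The size depends on assumed k and true AUC. For SUD versus control at N=50, the tilt toward the smallest fold is moderate: about 40% of wins against 28% for the largest fold, where 33% would be even. For relapse among 25 SUD patients there is no clear tilt; the damage there is that very small folds often give no AUC. The simulations hold true AUC equal across k. In practice a larger k also trains on more data, which is a further difference not due to the algorithm.

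The rule should be changed before modelling begins. Full rotation with pooled predictions, if that was meant, would remove most of the fold-size effect, and the text should then say so.

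**What to change.** Replace the last sentence of Data Preprocessing with wording such as:

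*One random partition of participants into folds, stratified by outcome label as far as class counts allow, will be drawn once with a single k and seed fixed in advance, and used for every algorithm. All folds will be rotated. The algorithm and its tuning will be chosen only within the training and validation folds of each rotation. Outer test-fold predictions will be pooled for the final AUC and F2. Algorithms will be compared by paired differences on the same participants.*

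The nesting matters: if folds were rotated without it, the same people could both select the algorithm and supply its final AUC, and the separation planned in Validation and Verification would be lost. With about 25 SUD patients and three latency labels, k must be small enough for stratification to be feasible. The randomization section should refer to this same partition.

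The cost is somewhat more computing and the loss of freedom to tune k by model. No new data are needed. The Results section reports data still at labelling and preprocessing as of June 2025, so on that status the change can precede modelling.

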### Algorithms

Modeling will be conducted using MATLAB, with ANN serving as the base algorithm. Additional algorithms, including decision trees, random forests, and support vector machines, will be used for validation. This multialgorithm approach will facilitate a comprehensive comparison of predictive accuracy across various models.

### Output

The primary objective of this study is to develop a MLM capable of predicting clinical outcomes in patients. To achieve this, the data will be segmented and classified into 5 categories (Figure 5). Around 2 of these categories will correspond to the first layer, which pertains to the duration of the therapeutic process, while the remaining 3 will focus on the latency of relapse, if any.

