**Figure 5 figure5:**
[figure not shown]
Model’s possible outputs. These categories will be used as output labels of the predictive model and will allow the evaluation of the patterns detected from the input.

For the duration of the therapeutic process, the following labels will be used:

Timely rehabilitation: patients with SUD who complete the rehabilitation protocol within 7 months.Late rehabilitation: patients with SUD who complete the protocol in 7 months or longer.

Regarding relapse latency, the labels will include the following:

Early relapse: substance use occurring within the first 6 months post discharge.Late relapse: substance use occurring after 6 months but before the completion of 18 months post discharge.One-year maintenance: patients who have abstained from substance use at the end of the 18-month postrecovery period.

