#### Predictive Model

A predictive model will be developed to distinguish between healthy individuals and patients with SUD. In addition, the model will predict the duration of a rehabilitation therapeutic program and the length of sobriety adherence for individuals rehabilitated using the center’s methodology. A minimum performance threshold of AUC≥0.8 and F2≥0.8 has been established to evaluate the model as fully functional.

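### Programme duration and relapse time are cut into five class labels for training and judging the model, although the aim includes predicting duration and length of sobriety and only about 25 patients carry these outcomes

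*Protocol article*

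**What the plan says.** The Predictive Model section under Outcomes states the aim as times: "the model will predict the duration of a rehabilitation therapeutic program and the length of sobriety adherence". The Output section then says that "the data will be segmented and classified into 5 categories", and the Figure 5 caption adds: "These categories will be used as output labels of the predictive model".

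The duration labels divide at 7 months; the first is "Timely rehabilitation: patients with SUD who complete the rehabilitation protocol within 7 months". The relapse labels begin with "Early relapse: substance use occurring within the first 6 months post discharge", followed by late relapse (after 6 and before 18 months post discharge) and maintenance (still abstinent at 18 months).

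Validation and Verification uses these categories as the benchmarks and sets the criterion: "Optimal model performance will be defined by achieving an area under the curve (AUC) of ≥0.80 and F2 score of ≥0.8".

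Two other statements bear on the point. The MLMs section names both classification and regression models. Principal Findings words the aim as estimating the duration of rehabilitation and the chance of an early relapse, a late one or none.

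**The concern.** A label keeps only the side of a cut on which a patient falls. Relapse at 1 month and at 5.9 months count as the same outcome, while 5.9 and 6.1 months count as different ones. Completing the programme just before and just after 7 months is treated in the same way.

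The loss matters here because controls contribute nothing to these outcomes. The minimum is 25 SUD patients (Sample Size), of whom 18 were enrolled by June 2025 (Results). Features are to be filtered by their correlation with the target (Data Preprocessing), so a coarse target weakens that step before any model is trained. The classes are also small, and the folds held out for validation and testing make them smaller. Finally, an abstinent patient whose follow-up stops before the label's horizon fits no relapse class, although his abstinent time is informative.

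**Working it through.** There is no figure in the plan to reproduce. The 80% power under Sample Size belongs to the comparison of SUD and control means, and no power is set for prediction. Power for one feature is used below as a measure of information lost.

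**Inputs from the document:** 25 SUD patients; duration cut at 7 months; relapse cut at 6 months; horizon 12 months (follow-up in the Abstract and Timeline) or 18 months (labels); 60% relapse (Introduction).

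**Assumptions:** two-sided 5% test; one standardised feature; correlation r with duration of 0.3 to 0.6; 50%, 70% or 85% of patients on one side of the 7-month cut; hazard ratio (HR) per SD of 1.5 to 2.5; constant hazard; relapse 40% to 80%.

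**Class sizes.** With 60% relapse, abstinence at the horizon is 0.4, so 25 × 0.4 = 10 patients are in maintenance. Ignoring differences between patients:
- 12-month horizon: early 25 × (1 − 0.4^(6/12)) = 9.2; late 15 − 9.2 = 5.8.
- 18-month horizon: early 25 × (1 − 0.4^(6/18)) = 6.6; late 15 − 6.6 = 8.4.

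**Duration.** For a normal outcome, cutting at quantile z with a fraction p on one side multiplies the correlation by φ(z)/√(p(1−p)):
- 50:50: 0.399/0.500 = 0.80
- 70:30: 0.348/0.458 = 0.76
- 85:15: 0.233/0.357 = 0.65

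Squared, these are about 0.64, 0.58 and 0.43, so 25 patients carry the information of roughly 16, 14 and 11. Simulated power in % (4,000 runs; Pearson test on the full scale → t-test on the split; loss in brackets):

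| r | 50:50 | 70:30 | 85:15 |
|---|---|---|---|
| 0.3 | 31.2 → 21.0 (10.2) | 31.8 → 19.8 (12.0) | 30.6 → 13.4 (17.2) |
| 0.4 | 52.2 → 35.4 (16.8) | 52.7 → 31.8 (20.9) | 52.7 → 22.6 (30.1) |
| 0.5 | 75.4 → 54.0 (21.4) | 74.2 → 47.8 (26.4) | 73.8 → 35.0 (38.8) |
| 0.6 | 91.3 → 72.2 (19.1) | 90.2 → 65.7 (24.5) | 91.8 → 49.8 (42.0) |

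The loss is 10 to 26 points for splits from 50:50 to 70:30, and 17 to 42 at 85:15.

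**Relapse.** Simulated power in % at n=25, 60% relapse and a 12-month horizon (2,500 runs; loss against Cox in brackets):

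| HR per SD | Cox score test | Three labels, unordered (ANOVA) | Three labels, ordered (Spearman) |
|---|---|---|---|
| 1.5 | 31.1 | 21.2 (9.9) | 26.7 (4.4) |
| 1.8 | 56.4 | 40.2 (16.2) | 49.2 (7.2) |
| 2.0 | 68.1 | 52.1 (16.0) | 62.0 (6.1) |
| 2.5 | 87.6 | 73.0 (14.6) | 81.3 (6.3) |

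Over 40% to 80% relapse and both horizons:
- Unordered: from 23.4 − 17.1 = 6.3 to 79.5 − 57.9 = 21.6 points.
- Ordered: from 24.0 − 22.1 = 1.9 to 79.9 − 66.8 = 13.1 points.

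With no effect, the Cox test rejected in 5.4% to 6.1% of runs and the label tests in 4.8% to 5.1%, so the Cox advantage is overstated by about a point.

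**On the plan's own metric.** In a simulation at n=25, training on full-scale duration and scoring the 7-month label raised out-of-sample AUC by about 0.02 to 0.05. The gain depends on the assumed number and strength of features, and is smaller if a strongly skewed duration is fitted untransformed.

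**The case against.** Several objections have force.

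- **The relapse aim is also stated in categories.** Principal Findings asks for early, late or no relapse. A reader might infer that the labels contradict the aim outright; for relapse they do not. The mismatch is with the Predictive Model wording, and for duration with Principal Findings too.
- **Regression is named.** True, but no regression target or error measure follows, and the output labels, benchmarks and success criterion are all categorical. That is a stated choice, not a detail left to a fuller document.
- **Order and dates are not specified.** A reader might infer from AUC and F2 that the labels are unordered. Nothing says so, and with ordered modelling most of the relapse loss disappears. Nor does the article promise relapse dates: Withdrawal Criteria excludes the corresponding data when exact timing cannot be determined, which shows only that timing is sought. Coarse dating would shrink the gain.
- **Power is not the plan's criterion.** A reader might take a loss such as 15 to 30 points as a property of this study. The documents support no such figure: it depends on assumed associations and splits, and the relapse loss never came near 30.
- **The 7-month cut may have programme meaning,** and durations may cluster. That is a reason to report the category, not to train only on it.
- **Censoring is not free.** Withdrawal Criteria discards the data of voluntary dropouts and of participants with excessive non-use of the band. This stands, and it limits the remedy.

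**Conclusion.** The concern holds as a lossy analysis choice that should be changed. The plan trains and judges on cut versions of two times, although its stated aim includes the times themselves and about 25 patients carry them. The direction of the loss is clear; its size is conditional on assumptions. At n=25 it is roughly 10 to 26 points of single-feature power for duration with splits up to 70:30, and up to 42 at 85:15. For relapse it is roughly 6 to 22 points with unordered labels and about 2 to 13 with ordered ones. These figures rest on a normal duration, a constant relapse hazard, exactly observed times and association strengths that the documents do not give. They measure lost information and do not forecast whether the model will reach its AUC and F2 thresholds.

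**What to change.** 1. Run the feature filter and train on programme duration in days, and on time from discharge to first use, recorded to the nearest date available. Censor abstinent patients at the end of their retained follow-up.
2. Derive the five categories by cutting the predictions at the same points. Keep AUC and F2 on those categories, and add a prediction error for duration and a C-index for relapse.
3. Where a relapse can be placed only in a class, model the three labels as ordered.
4. Reconcile the 12 months of post-discharge follow-up (Abstract, Timeline) with the 18-month relapse and maintenance labels (Output). As written, maintenance cannot be observed within the stated follow-up.

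The cost is an extra performance measure, some code and revised wording. Recruitment runs to January 2027, so the change can precede final modelling. Patients whose data are discarded under Withdrawal Criteria still cannot contribute censored time unless that data-handling rule is changed.

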**Figure 5 figure5:**
[figure not shown]
Model’s possible outputs. These categories will be used as output labels of the predictive model and will allow the evaluation of the patterns detected from the input.

For the duration of the therapeutic process, the following labels will be used:

Timely rehabilitation: patients with SUD who complete the rehabilitation protocol within 7 months.Late rehabilitation: patients with SUD who complete the protocol in 7 months or longer.

Regarding relapse latency, the labels will include the following:

Early relapse: substance use occurring within the first 6 months post discharge.Late relapse: substance use occurring after 6 months but before the completion of 18 months post discharge.One-year maintenance: patients who have abstained from substance use at the end of the 18-month postrecovery period.

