**Figure 1 figure1:**
[figure not shown]
Timeline of experimental procedures. (A) Demographic and psychological assessment, a battery of interviews and tests will be applied at 2 timepoints. (B) Digital measurements with the smart band Xiaomi Redmi Smart Band 8, starting on day one for controls, and after the first month of treatment for substance use disorder. (C) Evaluation of the emotional state during craving halfway through the digital monitoring period (third month), and at the end of it. (D) Data preprocessing is required for all 3 data sources. (E) Training in a machine learning predictive model in neural networks. (F) creation of a graphic user interface for clinical use.

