#### Graphical User Interface

As an outcome of this study, a graphical user interface will be developed using MATLAB to enable practical application of the predictive tool within the rehabilitation center where this research is being conducted. The graphical user interface will facilitate clinical use of the model and allow for further training and refinement, expanding its potential utility in similar settings.

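### Both therapy-duration labels require completing the programme, so an enrolled patient who leaves or uses before completion has no duration outcome and the duration model describes completers only

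*Protocol article*

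**What the plan says.** All references are to the protocol article.

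- **Output** states that "the data will be segmented and classified into 5 categories": two for the duration of the therapeutic process and three for relapse latency. The Figure 5 legend adds that "These categories will be used as output labels of the predictive model".
- **Duration labels (below Figure 5).** "Timely rehabilitation: patients with SUD who complete the rehabilitation protocol within 7 months" and "Late rehabilitation: patients with SUD who complete the protocol in 7 months or longer".
- **Relapse labels (same place).** "Early relapse: substance use occurring within the first 6 months post discharge"; "Late relapse: substance use occurring after 6 months but before the completion of 18 months post discharge"; and a maintenance label judged at the end of a post-recovery period.
- **Predictive Model (Outcomes)** lists a healthy-versus-SUD output, the duration of the programme, and the length of sobriety for individuals rehabilitated with the centre's method.
- **Goal and Objectives** and the abstract's Objective set the target as patients with SUD, with no restriction to completers. **Recruitment** enrols them while they are in the programme.
- **Withdrawal Criteria** withdraws a participant at once on relapse and discards the data of those who drop out of the study. **Data Exclusion** terminates participation on substance use, and removes a participant whose missing and excluded data exceed 20% of the 6-month period.
- **Graphical User Interface:** "The graphical user interface will facilitate clinical use of the model" at the same centre.

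**The concern.** Completion is not known when a patient enrols, nor when a clinician would consult the tool. A duration label that exists only for those who go on to complete makes the training and test sets depend on a future event. At the point of use the model would be applied to everyone in treatment, including those who will leave or use first, and it has no output that is correct for them.

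Two things are at stake. First, the AUC and F2 thresholds of 0.80, which decide whether the model counts as fully functional and, for the AUC, whether the interface is built, could be met without the duration output ever being tested on a non-completer. Second, a tool meant to support decisions during rehabilitation would say nothing about whether the patient will finish, while appearing to answer a question about how his rehabilitation will go.

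**Working it through.** **1. Count the labels.** Output announces five: 2 + 3. The list below Figure 5 has timely, late, early relapse, late relapse and maintenance, again 2 + 3 = 5. The set is closed, and the text gives the wording of every label, so the missing figure image is unlikely to hold a sixth.

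**2. Test each label on a participant who leaves the programme at month 3 and is willing to stay in the study.**

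| Label | Condition | Open to him? |
|---|---|---|
| Timely rehabilitation | completes within 7 months | no |
| Late rehabilitation | completes in 7 months or longer | no |
| Early relapse | use in first 6 months after discharge | only if leaving counts as discharge |
| Late relapse | use after 6 and before 18 months after discharge | only if leaving counts as discharge |
| Maintenance | abstinent at end of post-recovery period | only if leaving counts as recovery |

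Duration: 0 of 2. Relapse latency: 0 of 3 if discharge means discharge on completion, otherwise open. The word post-recovery in the maintenance label, and the restriction to rehabilitated individuals under Predictive Model, both point to completers.

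**3. Test a participant who uses during the stay.** He has not completed, so he has no duration label. His use precedes discharge, so it meets neither relapse definition. He is also withdrawn.

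**4. Check whether the data would survive.** The removal limit is 20% of 6 months: 0.20 × 6 = 1.2 months. A participant whose band data stop before month 6 − 1.2 = 4.8 therefore exceeds the limit if the remaining time counts as missing. For the month-3 leaver who stops wearing the band, 3/6 = 50% is missing. New label wording alone would not bring him back.

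**5. Direction of the effect.** Let C be completion, T timely completion and x the predictors. The quantity relevant to a patient in treatment is

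P(T and C | x) = P(T | C, x) × P(C | x).

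A duration model built on completers estimates only P(T | C, x). Since P(C | x) is at most 1, that is too high wherever P(C | x) is below 1 and timely completion is possible. This holds whatever the predictor mix, provided the model is well calibrated among completers.

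**6. Illustration; the rates are assumptions.** The protocol gives no non-completion rate d, so take 20% to 50%. With the minimum of 25 SUD participants, those without a duration label number 25 × 0.20 = 5 to 25 × 0.50 = 12.5. If 70% of completers finish within 7 months (also assumed), the share of all in-treatment patients who do so is 0.70 × (1 − d): 0.70 × 0.80 = 56% and 0.70 × 0.50 = 35%.

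A statement that needs no timely share: every timely or late output for a non-completer is wrong by definition, so the proportion of correct duration outputs among all patients cannot exceed 1 − d, which is 80% to 50% over the same range, however good the model is among completers.

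**The case against.** **Relapse labels and the third output.** A reader might infer that an early leaver has no output label at all, and that the whole tool is trained only on completers. The text does not support that. Discharge is undefined; if leaving counts, a followed leaver can receive a relapse label. The healthy-versus-SUD output does not need completion and could use his data. The firm claim is confined to the duration layer, with the relapse layer probable.

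**Declared scope.** The sobriety prediction is explicitly for rehabilitated individuals, and duration among completers is a legitimate, narrower target. This stands for the relapse layer. It does not reconcile the duration labels with a goal and an interface that speak of patients with SUD in general. Nor do the documents say that non-completion is a failure of rehabilitation; the point does not depend on that.

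**Start of band wear.** The Figure 1 legend has SUD band data "starting on day one for controls, and after the first month of treatment for substance use disorder". One could read this as further selection, since first-month leavers give no band data. But Timeline synchronises bands at the baseline session, so study baseline may simply fall at treatment month 1, and 1 + 6 months matches the 7-month cut. That is a landmark start, with first-month leavers never enrolled, and it is not used against the plan here.

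**Size.** The 20% to 50% and the 70% have no source in the documents, 25 is a minimum that recruitment aims to exceed, and nothing says the interface will display a probability. A reader might take the gap between 70% and 56% or 35% as the bias clinicians will see. The documents do not support that; only the direction is established.

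**Fuller documents.** The article condenses a longer protocol, and handling of unlabelled cases could sit there. But the closed label set is stated here, so this is a rule that excludes an outcome, not a detail left out.

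**Conclusion.** The point holds for the duration output: both labels require completion, the set is closed, and an enrolled SUD participant who leaves or uses before completing has no duration label. For the relapse output it is probable but turns on the undefined discharge. It does not extend to the healthy-versus-SUD output.

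As written, the AUC and F2 for duration would describe completers only, while the stated target is patients with SUD and the intended use is at the centre. The size cannot be determined from the documents. The direction, too high a predicted share of timely completion among patients in treatment, follows for any non-completion above zero, assuming calibration among completers. The change should be made, and there is time: recruitment runs to January 2027, and 18 SUD participants had been enrolled by June 2025.

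**What to change.** 1. In Output and Figure 5, add a first-layer category for participants who did not complete (left, or used, before completion). Alternatively use timely completion versus not timely, reporting late completers and non-completers as subtypes.
2. Define the discharge date that starts the relapse clock, for completers and non-completers alike, and use the same origin in all three relapse labels.
3. Reconcile the new labels with Withdrawal Criteria and Data Exclusion, so that data collected before leaving or use are kept for labelling where consent allows. This concerns study data, not treatment.
4. Report AUC and F2 for all enrolled SUD participants as well as for completers.
5. If non-completers are not to be labelled, restrict the stated target population, and what the interface claims, to programme completers.

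**Cost.** Label and analysis wording, a change to the data-retention rules, and recording the date and reason of leaving. An inpatient centre probably holds these, but the article does not say so. The extra class may be small, or mixed if merged with late completion, and the measured performance may be less favourable. A merged class also partly replaces the duration target with a composite, which is why the subtypes should be shown.
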